**Fig. 1 Fig1:**
[figure not shown]
Stepped wedge, cluster randomized controlled trial study design. Each cell represents five or six clusters, and a data collection point. Twenty-two clusters with approximately 4,275 birth notifications will be assessed for eligibility, randomized, and allocated to the intervention or control groups. At the time point 0 months, the baseline evaluation will occur. At the time point 6 months, five clusters will be randomized to receive the intervention. By the time point 24 months, all clusters will be receiving the intervention

**Fig. 2 Fig2:**
[figure not shown]
Trial profile

### Inclusion and exclusion criteria

Thirty-seven birthing hospitals are located in WA; 28 public (one tertiary maternity hospital and 27 secondary hospitals) and nine private birthing hospitals. All public birthing hospitals in WA with five or more annual births of Aboriginal babies will be invited to participate in the intervention. All Aboriginal mothers who give birth to a live baby will be invited to participate in the study. Mothers will be asked for their written informed consent to be part of the study and to have evaluation data collected. We will not exclude any women who deliver a preterm baby, babies who develop complications, or any unwell babies, as these babies are most likely to benefit most from the improved skills of their primary care workers.

### Blinding

All intervention and control clusters will be blinded to the specific process outcomes that will be evaluated. However, blinding the clusters to the intervention and to the clinical outcomes will not be possible because they will be aware of the study protocol.

### Development of project tools

We will first develop generic guidelines, protocols, and tools for all components of the intervention: hospital consultation, families, and primary care providers. We will test and adapt all tools during a pilot phase in one pre-trial maternity hospital.

### Randomization

A stepped wedge, cluster randomized controlled trial design was chosen in which hospitals are allocated into geographical clusters and then randomized into two groups (intervention or control) within each of the five steps (Fig. 1). Twenty-five birthing hospitals included in the sampling frame have been grouped into 22 geographical clusters defined by postcode. As such, these clusters are the unit of randomization in this trial. The cluster randomization was completed using a random number generator in Excel. A member of the research team grouped the 25 hospitals into 22 clusters and labelled these clusters 1 to 22. A separate Excel spreadsheet was created with a column containing the numbers 1 to 22. No information about the corresponding hospitals was present in this document. The de-identified Excel file was given to our statistician, who was blinded to the corresponding cluster information. The random number generator was used to generate a number from 0 to 1 next to each number in the column containing the de-identified cluster data (numbers 1 to 22). The two columns were then sorted by the column containing the random number, from the smallest to the largest. Five steps are included in this stepped wedge design, each representing 6 months. During the first step, or the first 6 months, all clusters are controls. Allocation into the intervention or control group for the additional four steps is as described below. Using the sorted list provided by the statistician, the first five clusters were allocated to the intervention group in step 1. Once allocated to the intervention group, a cluster continues in the intervention group for the remainder of the trial. The remaining 17 clusters are allocated to the control group for step 1. For step 2, the six clusters that immediately follow the first five clusters in the list were allocated to the intervention group. In total, 11 clusters were allocated to the intervention group by step 2. The remaining 11 clusters were allocated to the control group. The next five clusters in the random number generator sorted list were allocated to the intervention in step 3. The remaining six clusters were allocated to the control group. The final six clusters were allocated to the intervention group in step 4. The intervention commencement will be staggered at 6 monthly intervals, and all clusters will receive the intervention by step 4.

### Sample size calculation

The proposed sample size calculation is based on our primary hypothesis that the new model of care will result in a significant reduction in all-cause hospitalization in infants aged 0 to < 3 months of age. Our pilot data indicate that the approximate number of Aboriginal babies delivered in the birthing hospitals included in the sampling frame is 1,900 per year. We therefore anticipate approximately 4,750 Aboriginal births during the 30-month trial period. Of these, approximately 2,375 will be born in the control setting, and 2,375 in the intervention setting. All families delivering within the hospitals implementing the intervention will have the opportunity to participate in the trial. We estimate a 20 % refusal and loss to follow-up rate within the intervention group. Thus, we anticipate approximately 1,900 Aboriginal infants born over a 30-month period will be involved in the intervention. In total, approximately 4,300 Aboriginal infants will be followed up in the trial. Twenty-five hospitals with maternity units in WA comprise 22 distinct geographical clusters, with an average of 39 anticipated births per cluster per 6-month step. The average current prevalence of any (all cause) hospitalization in infants aged 0 to < 3 months is 31 %. Early data indicate that hospitalization rates range from 15 to 50 % across the clusters. Estimation of the study power requires calculation of the design effect, which, in the context of a stepped wedge design, is the factor which must be applied to the total number of subjects required in a similarly powered individual-level parallel group design to give the number of subjects per step in a stepped wedge design. We calculated the intracluster correlation (ICC) based on previous hospitalization rates. The calculated ICC of 0.017 was used in the Woertman et al. [28] formula to calculate the design effect with the outcome being 0.57. With 4,300 babies followed up over the 30-month period, the study will provide 80 % power to detect, at a significance level of *P* < 0.05, a reduction in prevalence of any early hospitalization of 31 % to 24.5 % because of the intervention.

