### Data analysis

Data analysis will be conducted on the basis of intention to treat, regardless of movement between clusters. The intervention effect will be estimated by the between-cluster (those awaiting the intervention and those receiving the intervention) and within-cluster (before and after) comparisons. An analysis of the primary outcome (any hospitalization in the first 3 months of life) will be conducted at the individual infant level and will use binary logistic regression incorporating generalized estimating equations (GEE) to account for the loss of independence due to clustering. The primary independent variable will be whether or not the baby received the intervention. This will give rise to an odds ratio for the effect of the intervention on the probability of early hospitalization. The analysis will adjust for individual covariates, for example, maternal age, which may differ between groups receiving or not receiving the intervention at a given step. Similar techniques will be used for comparison of emergency department presentations and immunization coverage.

A societal viewpoint will be taken for the economic evaluation where all costs and consequences to the mothers and the wider community will be considered. All direct (fixed and variable) costs will be considered and will include the monetary costs of the intervention and resources. Consequences will be measured as hospitalizations averted. Incremental direct costs will be calculated by comparing the costs generated by the intervention with the costs generated by the control arm of standard care. Incremental consequences will be calculated by comparing the number of hospitalizations in the intervention clinics with the number of hospitalizations in the control clinics. Incremental cost-effectiveness ratios (cost per infant hospitalization case averted) will be calculated by dividing the incremental direct costs by the incremental hospitalization cases averted. Sensitivity analysis (a method to determine the robustness of an assessment by examining the extent to which results are affected by changes in methods, values of variables or assumptions) will also be performed. Satisfaction with care will also be assessed descriptively. The process outcomes and implementation of the intervention will also be assessed descriptively.

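### The 80 % power counts only intervention infants who take part and gives all of them the full effect; if refusers are analysed by intention to treat, it falls below 80 %, to about 65 % at worst

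*Protocol article*

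**What the plan says.** All of the following is from the protocol article.

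- **Sample size calculation, births.** "We therefore anticipate approximately 4,750 Aboriginal births during the 30-month trial period". These are split evenly: 2,375 in the control setting and 2,375 in the intervention setting.
- **Sample size calculation, attrition.** A single figure of 20 % is given as the "refusal and loss to follow-up rate within the intervention group". It leaves 1,900 infants in the intervention. No such deduction is made for controls.
- **Sample size calculation, power.** "With 4,300 babies followed up over the 30-month period, the study will provide" 80 % power for "a reduction in prevalence of any early hospitalization of 31 % to 24.5 % because of the intervention". The ICC is 0.017, the design effect 0.57, and 39 births are expected per cluster per step.
- **Data analysis.** "Data analysis will be conducted on the basis of intention to treat, regardless of movement between clusters". The same paragraph then makes the main independent variable the individual baby's receipt of the intervention.
- **Randomization.** The geographical cluster is the randomized unit.
- **Data collection.** Hospitalization comes from routine systems, for control and intervention groups alike.
- **Ethical issues.** In intervention clusters, mothers are asked for written consent to take part and to have evaluation data collected. In control clusters, where individual consent cannot be taken, linked data without identification will be requested.

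**The concern.** When clusters are randomized and the analysis is by intention to treat, a baby born in a cluster that has crossed over belongs to the intervention condition whether or not the family accepts. A refusing family does not shrink the sample. It stays in and pulls the intervention-setting rate back towards 31 %. The sample size section does the opposite: it shrinks the count and leaves the effect whole.

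The two treatments of refusal cost very different amounts of power. Losing 20 % of one arm at random is mild. Keeping 20 % of that arm untreated shrinks the effect itself by a fifth. The Discussion relies on the 4,300 to claim sufficient power for all primary and secondary outcomes. If the primary analysis is in fact by allocation, a null result could be read as evidence against the intervention when the trial had less power than reported.

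**Working it through.** **Inputs.** From Sample size calculation: 31 % and 24.5 %, alpha 0.05 (taken as two-sided), ICC 0.017, 39 births per cluster per step, 4,750 births, and 20 % off the intervention side. From Trial design and Randomization: a baseline plus four steps, so five periods, and 22 clusters crossing over as 5, 6, 5 and 6.

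**1. The plan's counts.** 2,375 × 0.8 = 1,900. 1,900 + 2,375 = 4,275, the number in the Fig. 1 caption, rounded to 4,300 in the text. 4,275 / (22 × 5) = 38.9, so the 39 per cell also comes after the deduction. All 4,750 births would give 43.2 per cell.

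**2. The plan's design effect** (Woertman formula, k = 4 steps, one baseline and one measurement per step, n = 39):

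[1 + 0.017 × (156 + 39 − 1)] / [1 + 0.017 × (78 + 39 − 1)] × 3 × (1 − 0.017) / [2 × (4 − 1/4)]
= (4.298 / 2.972) × (2.949 / 7.5) = 0.569. The plan states 0.57.

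**3. The plan's sample size and power.** An individually randomized trial of 31 % vs 24.5 % needs 744 per arm, 1,488 in all. 1,488 × 0.57 × 5 = 4,241, close to 4,300.

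Power for a total N uses m = N / (5 × 0.57 × 2) per arm and
z = [d√m − 1.96 √(2p̄(1 − p̄))] / √(p₁(1 − p₁) + p₂(1 − p₂)).

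At N = 4,300, m = 754.4 and z = (0.065 × 27.47 − 1.241) / 0.632 = 0.86, giving 80.6 %. At 4,275 it is 80.3 %. The Hussey-Hughes variance with the actual roll-out and 39 per cell gives 80.4 %. The stated 80 % is therefore correct for 1,900 intervention infants who all carry the full 6.5 points.

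**4. Refusers kept in the analysis.** Assume that 24.5 % is the rate among recipients, that a fraction f of intervention-setting infants refuse, gain nothing and have outcomes, and that the remaining 0.20 − f are lost. The analysed intervention fraction is 0.8 + f, and the average effect is 6.5 × 0.8 / (0.8 + f).

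| Refusal f | Lost | N analysed | Effect (points) | Power |
|---|---|---|---|---|
| 0 % | 20 % | 4,275 | 6.50 | 80.3 % |
| 5 % | 15 % | 4,394 | 6.12 | 76.4 % |
| 10 % | 10 % | 4,513 | 5.78 | 72.5 % |
| 15 % | 5 % | 4,631 | 5.47 | 68.8 % |
| 20 % | 0 % | 4,750 | 5.20 | 65.3 % |

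In the last row the intervention-setting rate is 31 − 0.8 × 6.5 = 25.8 %. With m = 833.3, z = (0.052 × 28.87 − 1.250) / 0.637 = 0.39. Recomputing the design effect at 43.2 per cell gives 65.0 %, and Hussey-Hughes gives 64.9 %.

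**5. The other reading of 24.5 %.** If it is already the average over all intervention-setting births, N = 4,750 with d = 6.5 points gives z = 1.01 and power 84.3 %.

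**6. What 80 % power needs in 4,750 births.** Power is 80.6 % at 24.8 % and 79.3 % at 24.9 %, so about a 6.2-point reduction across all births. With 20 % non-uptake and no benefit to refusers, that is 6.2 / 0.8 = 7.75 points among acceptors.

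**The case against.** The strongest reply is that refusers may have no usable outcome. Consent in intervention clusters covers evaluation data, and de-identified linkage is described as the answer for control clusters. On that reading the 20 % are missing, as the sample size section counts them. This stands as an open point, because the Data collection section points the other way with routine data from both groups. It does not rescue the plan: dropping refusers on one side only is not intention to treat by cluster, and it brings in selection that the control side does not have.

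Second, the modelled exposure is individual receipt, which fits a full effect among recipients. That is true, but it shows the power matching one sentence of the Data analysis section and not the intention-to-treat sentence beside it.

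Third, zero benefit among refusers is an extreme assumption, since two of the three components in Table 1 work with hospitals and primary care providers. This stands. If all 20 % refuse, stay in, and gain half the effect, the average reduction is 0.9 × 6.5 = 5.85 points and power in 4,750 births is about 76 %.

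A reader might infer that power for 31 % to 24.5 % under intention to treat is simply 65 %. The document does not support that. The 65 % is power for 31 % vs 25.8 %, and a true 31 % vs 24.5 % contrast across all 4,750 births has 84 %. Nor does the document show that most of the 20 % is refusal, since it gives only one combined figure.

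**Conclusion.** The point holds as a mismatch between the contrast that was powered and the analysis principle that was declared. It is not an arithmetic slip: the design effect, the 4,300 and the 80 % all reproduce. They do so by removing the whole 20 % from the intervention count and giving the full effect to those who remain, which allows nothing for dilution.

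How far power falls under intention to treat depends on facts the article does not give. Where 24.5 % is the recipients' rate and refusers gain nothing, power lies between 80 % (all of the 20 % lost) and about 65 % (all of it retained non-recipients). If 24.5 % is the all-births rate, power with 4,750 births is about 84 % and the stated figure is conservative. The first reading fits the plan's own counts better, because the effect is paired with the 1,900 who take part, but neither is stated outright. No single figure can be called the plan's power until the two sentences in Data analysis are reconciled.

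**What to change.** 1. In Data analysis, define the primary exposure by the cluster's allocated status in the period of the baby's birth, in line with intention to treat. Any analysis by individual receipt becomes secondary.
2. In Sample size calculation, split the 20 % into refusal and loss of outcome data. State whether refusers' routine hospitalization data will be analysed, and align this with the consent wording in Ethical issues.
3. State whether 24.5 % is the rate among recipients or across all intervention-setting births.
4. Restate the power as a range. With 24.5 % among recipients and no benefit to refusers, give about 76 %, 73 % and 69 % at 5 %, 10 % and 15 % refusal with the rest lost, and about 65 % if all 20 % are retained non-recipients. With 24.5 % across all births, give about 84 % for 4,750. Add that 80 % power in 4,750 births needs about a 6.2-point reduction across all births, or about 7.75 points among acceptors at 20 % non-uptake.
5. Bring the power statement in the Discussion into line.

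This takes no added enrolment and no change to the roll-out. The only cost is that the stated power becomes less favourable, unless 24.5 % proves to be the all-births rate.

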### The intervention group

The targeted support and care coordination intervention is outlined in Table 1. Initially we will work with birthing hospitals to understand gaps in infant care coordination and target project tools to meet local needs. These consultations will inform the specifics of the care coordination activities, which will include the following:

**Table 1 Tab1:** Description of the intervention

The following three components of the intervention will be implemented by dedicated infant healthcare coordinators:
Hospitals - Work with birthing hospitals to understand gaps in infant care coordination and target project tools to meet local needs.
Families - Meet families as soon as acceptable to the families after birth. Use the locally targeted care coordination tools for the following:
- consult with families about their health care needs,
- provide information about primary care services available for the first 3 months of the baby’s life,
- offer assistance with birth and Medicare registration forms,
- consult with families about their choice for primary care provider,
- offer to notify the chosen primary care provider about the baby’s health needs, and
- offer assistance with health care coordination at the time of discharge from hospital.
Primary care providers - Work with the family’s chosen primary care provider to achieve the following:
- ensure they receive birth and hospital details,
- offer tools and guidance on early infant primary care, and
- offer additional assistance and contact points with experienced community child health nurses, primary care networks and pediatricians.

Assessing the needs and goals by consulting with families about their healthcare needs, their preferred primary care provider, and assistance with Australian Government forms (Medicare and birth registration)Facilitating transitions across settings by providing information to the families about the primary care services available for the first 3 months of the baby’s life, offering to contact the chosen primary care provider on behalf of the family, offering assistance with healthcare coordination at the time of discharge; and by offering additional assistance to primary care providers and contact points with experienced community child health nurses, primary care networks, and pediatriciansCommunication through interpersonal interactions with the families and primary care providers, and transferring information through direct contact between the hospital and chosen primary care provider, ensuring they receive birth and hospital details

Coordination activities will be led by dedicated infant healthcare professionals, who will meet with families as soon as acceptable after birth. Mothers will be asked for their written informed consent to be part of the study and to have evaluation data collected.

### The control group

The control clusters will be the hospitals and clinics located in clusters that have not yet received the intervention. The control clusters will receive standard care according to regional guidelines without additional support. The control clusters will receive the same level of evaluation data collection as the intervention groups.

### Data collection

Outcomes will measure the impact of the intervention from a systems perspective, including the quality of care, healthcare utilization and cost. Outcomes will also measure the process of the intervention from family and healthcare professional perspectives.

Information from routine data capture systems (midwives notification system, hospital morbidity database, emergency department database, Australian Immunisation Register (ACIR) database, and the Commonwealth Medical Benefits System (MBS) database) will be collected from both the control and intervention groups. These data will include the following: (i) sociodemographic data: obstetric history, age, sociodemographics, medical history, morbidities, birth weight, gestational age, Apgar score, and discharge date; (ii) hospitalization data from all WA hospitals on all-cause hospitalization and emergency department presentations; (iii) immunization data from ACIR (date of first and second doses of hepatitis B and date of first dose of DTP containing vaccine) from birth until the baby reaches 3 months of age; and (iv) Medicare data from the MBS (Date of Medicare registration and dates of child health checks (item number 715)) from birth until the baby reaches 3 months of age.

Economic evaluation will compare outcomes between the intervention and control groups. Consequences will be measured as the health gains from the child health assessments and immunizations received. Short-term health gains include reduced emergency department presentations and hospital admissions during the first 3 months of life. Long-term health gains include improved child neurodevelopment (especially speech delay, concentration, learning and educational outcomes) and reduced infectious disease (including gastroenteritis, Haemophilus influenzae type b (Hib), pneumococcal disease and pertussis).

Some data will be collected only in the intervention clusters. This will include questions from structured questionnaires querying the mother about her satisfaction with the healthcare she received during the antenatal and postnatal periods. Process data will also be collected on the needs and support required by the hospitals and primary care providers including IT resources, formal education sessions, guidelines and protocols distributed, and telephone calls. Economic data will include the full cost of implementing the intervention in each cluster. This will include the costs of the new intervention including all aspects of delivery, tools, training visits (including vehicle hire, petrol, accommodation, meals) telephone calls, and dedicated staff salaries.

### Data analysis

Data analysis will be conducted on the basis of intention to treat, regardless of movement between clusters. The intervention effect will be estimated by the between-cluster (those awaiting the intervention and those receiving the intervention) and within-cluster (before and after) comparisons. An analysis of the primary outcome (any hospitalization in the first 3 months of life) will be conducted at the individual infant level and will use binary logistic regression incorporating generalized estimating equations (GEE) to account for the loss of independence due to clustering. The primary independent variable will be whether or not the baby received the intervention. This will give rise to an odds ratio for the effect of the intervention on the probability of early hospitalization. The analysis will adjust for individual covariates, for example, maternal age, which may differ between groups receiving or not receiving the intervention at a given step. Similar techniques will be used for comparison of emergency department presentations and immunization coverage.

A societal viewpoint will be taken for the economic evaluation where all costs and consequences to the mothers and the wider community will be considered. All direct (fixed and variable) costs will be considered and will include the monetary costs of the intervention and resources. Consequences will be measured as hospitalizations averted. Incremental direct costs will be calculated by comparing the costs generated by the intervention with the costs generated by the control arm of standard care. Incremental consequences will be calculated by comparing the number of hospitalizations in the intervention clinics with the number of hospitalizations in the control clinics. Incremental cost-effectiveness ratios (cost per infant hospitalization case averted) will be calculated by dividing the incremental direct costs by the incremental hospitalization cases averted. Sensitivity analysis (a method to determine the robustness of an assessment by examining the extent to which results are affected by changes in methods, values of variables or assumptions) will also be performed. Satisfaction with care will also be assessed descriptively. The process outcomes and implementation of the intervention will also be assessed descriptively.

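### GEE on 22 clusters, if run in its usual uncorrected form, tests at about 8% to 10% rather than 5%, and the protocol mentions no small-sample correction

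*Protocol article*

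**What the plan says.** The Data analysis section specifies, for any hospitalization in the first three months, a logistic model at infant level, "incorporating generalized estimating equations (GEE) to account for the loss of independence due to clustering". It extends similar techniques to emergency department presentations and immunization coverage. It names no variance estimator, working correlation, reference distribution or small-sample correction.

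The Randomization section fixes the number of independent units: "Twenty-five birthing hospitals included in the sampling frame have been grouped into 22 geographical clusters defined by postcode". These cross over in groups of 5, 6, 5 and 6.

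The 5% level (P < 0.05) appears under Sample size calculation, in the claim of 80% power. The effect to be detected there is "a reduction in prevalence of any early hospitalization of 31 % to 24.5 % because of the intervention". Sidedness is not stated; I take it as two-sided.

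On cluster size, the article gives only an average ("with an average of 39 anticipated births per cluster per 6-month step") and an entry floor for hospitals: "All public birthing hospitals in WA with five or more annual births of Aboriginal babies will be invited to participate in the intervention".

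**The concern.** The validity of robust GEE inference depends on the number of clusters, here 22, and not on the roughly 4,300 infants. With so few clusters the ordinary sandwich variance is biased downward and is itself variable. A z test ignores both problems, and unequal cluster sizes make them worse.

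At stake is the primary conclusion. If the named method is run with common defaults, a positive result carries more than the stated 5% false-positive risk and the interval for the odds ratio is too narrow. The secondary outcomes analysed in the same way would share the fault.

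**Working it through.** **1. The plan's own figures.** The stated design effect comes from "The calculated ICC of 0.017 was used in the Woertman et al. [28] formula to calculate the design effect with the outcome being 0.57". With 4 steps, 1 baseline period, 1 measurement per step, n = 39 and ICC = 0.017:

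- [1 + 0.017 × (156 + 38)] / [1 + 0.017 × (78 + 38)] = 4.298 / 2.972 = 1.446
- 3 × (1 − 0.017) / [2 × (4 − 1/4)] = 2.949 / 7.5 = 0.3932
- product = 0.569, against 0.57 stated.

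An individually randomized comparison of 31% with 24.5% needs 744 per arm, or 1,488 in all. Then 1,488 × 0.5686 × 5 periods = 4,231, against about 4,300 stated. Power at 4,300 is 80.6%. The sample-size figures reproduce. They rest on a normal reference.

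**2. What is known about cluster size.** 1,900 births a year / 22 clusters = 86 per cluster-year. 4,300 / (22 × 5) = 39 per cluster-period. The hospital floor of five a year is 2.5 per six-month period. No actual cluster sizes are given, so the CV has to be assumed and varied.

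**3. Type I error under no effect.** Design simulated: 22 clusters crossing 5/6/5/6, five periods, mean 39 per cell, risk 31%, ICC 0.017, normal random cluster intercept, logistic GEE with exchangeable working correlation and period effects. There were 6,000 trials per scenario (simulation error about ±0.7 points). Rejection rate (%) at nominal two-sided 5%, by realized size CV:

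| Variance and reference | CV 0 | CV 0.7 | CV 1.0 | CV 1.2 |
|---|---|---|---|---|
| Uncorrected sandwich, z | 8.2 | 8.5 | 9.8 | 10.6 |
| Uncorrected sandwich, t(20) | 6.6 | 6.8 | 8.0 | 8.6 |
| Kauermann-Carroll, t(20) | 5.4 | 5.1 | 6.2 | 6.5 |
| Mancl-DeRouen, z | 5.8 | 5.2 | 5.9 | 5.8 |
| Mancl-DeRouen, t(20) | 4.2 | 3.9 | 4.5 | 4.6 |
| Model-based, z | 5.4 | 5.5 | 6.2 | 6.5 |

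A separate simulation (2,500 replicates, beta-distributed cluster effects, lognormal sizes) gave 8.1% with equal clusters and 9.6% to 10.1% at an assumed CV of 0.8 to 1.2 for the uncorrected z test.

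**4. Sensitivity of the uncorrected sandwich z test.**

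- No period effects fitted: 7.2% to 8.8% (CV 0 to 1.0).
- ICC 0.038: 7.5% to 9.7%.
- 30% of the between-cluster variance at cluster-period level: 8.3% to 10.8%.
- Independence working correlation with period effects: 8.3% to 15.7%.

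No uncorrected sandwich setting reached 5%, even with t(20); the lowest was 5.8%, without period effects.

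**5. Why both parts of a correction matter.** In the 2,500-replicate simulation the empirical SD of the log odds ratio was 0.112 (equal clusters) and 0.119 (CV 0.8), against a mean robust standard error of 0.105 in both. The ratios are 0.105/0.112 = 0.94 and 0.105/0.119 = 0.88, so intervals are about 6% and 12% too short on average. This bias alone would give about 2 × [1 − Φ(1.96 × 0.9375)] = 6.6% and 2 × [1 − Φ(1.96 × 0.882)] = 8.4%. I attribute most of the remainder to the variability of the estimated standard error, which the t reference addresses.

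**6. Power cost of the t reference.** Power of 80.6% corresponds to 0.865 + 1.960 = 2.825 standard errors. Replacing 1.960 by the t(20) value 2.086 gives Φ(2.825 − 2.086) = Φ(0.739) = 77%. Starting from exactly 80%, Φ(0.842 + 1.960 − 2.086) = Φ(0.716) = 76%.

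**The case against.** The strongest objection is that the article does not commit to the uncorrected sandwich. It says GEE and no more. The variance estimator and degrees of freedom are commonly settled in an SAP, which is not shown, and a bias-corrected GEE is still GEE as written. Analyses that all fit the wording range from about 4% to above 10%. A reader might infer that the planned test runs at 8% to 10%, but the document does not support that. The figure belongs to one implementation, though it is the usual one.

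A reader might also infer that the clusters are known to be very unequal and the false-positive risk therefore doubled. That is not supported either. The five-birth floor applies to hospitals, not clusters, and does not show that any hospital is that small. No number of Aboriginal births is given for the tertiary hospital. The figure near 10% depends on an assumed CV; the figure near 8% does not.

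Model-based standard errors with a z test come close to nominal in the table, but only because the simulated correlation was the one fitted. With some cluster-period variance they give 7.5% to 9.5%, and under an independence working structure with period effects and ICC 0.017, 20% to 30%.

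What survives is that the method, the 22 clusters and the 5% level are all fixed, and the conventional way of running that method on that design misses 5% even in the most favourable case of equal clusters. That goes beyond an absent detail.

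**Conclusion.** The point holds as a conditional one. GEE on these 22 clusters with the uncorrected sandwich variance and a z test has a two-sided type I error of about 8% with equal clusters, and about 10% if sizes vary widely (8.5%, 9.8% and 10.6% at CV 0.7, 1.0 and 1.2). The main figures assume ICC 0.017, exchangeable working correlation and fitted period effects, which the article does not mention; without them the error is 7.2% to 8.8%. The sample-size arithmetic is not in error on this point. If the SAP already specifies a correction, confirming that closes the matter.

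**What to change.** State in the Data analysis section, or confirm in the SAP before outcome data are seen, that the primary GEE test and confidence interval use a small-sample bias-corrected variance with a t reference on about 20 df (22 clusters minus 2). Either of these would serve:

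- Kauermann-Carroll, with size about 5% to 6.5%;
- Mancl-DeRouen, with size about 4% to 5%, slightly conservative.

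Apply the same to emergency department presentations and immunization coverage. Name the working correlation in the same sentence, because the sizes above are for an exchangeable structure. Under independence with period effects, the t(20) versions reach 8.8% (Kauermann-Carroll) and 5.9% (Mancl-DeRouen) at CV 1.2.

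The change is one sentence and leaves design and data collection alone. The cost is power: from 80% to about 77% from the t reference alone, and somewhat further from the larger corrected standard error, which I have not quantified.
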